#### 9.2.4 AE report

- ✧ The investigators need to fill out the AE record form in CRF.
- ✧ The data retained in CRF will be forwarded to the clinical trial monitors by the end of this trial.

#### 9.2.5 Handling of AE during and after the trial period

The investigators should observe and record the outcomes of all AEs and follow up with the subjects who withdraw from this trial due to AE until the AE is resolved completely. The investigators must determine whether the AE is related to the study drug and provide evidence to support the opinion.

### 9.3 Severe adverse events (SAE) and unexpected adverse drug reactions (UADR)

9.3.1 Definition: SAE is one of the adverse events below and might occur at any doses:

- ✧ Causing death
- ✧ Life-threatening
- ✧ Requiring hospitalization or prolonged stay in hospital
- ✧ Causing long-term or significant disability, or affecting working and living capabilities
- ✧ Causing congenital malformations

“UADR” refers to an adverse reaction, the nature or severity of which is not consistent with the applicable product information.

### 9.3.2 SAE reporting

- ✧ All SAEs must be notified by phone or fax within 24 hours to the principal investigator: [name] [[contact], [contact]], Department of Dermatology and Venereology, Peking University First Hospital and the supervisor of this clinical study sponsor: [name] [[contact], [name], [contact]], and reported to SFDA and local Food and Drug Administration of the provinces, autonomous regions and municipalities.
- ✧ The complete SAE Report Form should be filled within 3 days and submitted to the sponsor's clinical study monitors, the principal investigator and the Medical Ethics Committee of Peking University First Hospital for record-filing purpose.
- ✧ If the AE is severe and life threatening, the written event summary should be submitted to the relevant regulatory authority within 7 days; if the AE is severe but not life threatening, the summary can be submitted within 15 days.

### 9.3.3 Opening the emergency letters and unblinding:

Blinding should be well kept throughout the study. However, in case of emergency and when it becomes really necessary to identify the type of drug a patient has received, the principal investigator of the study institution can open the emergency letter (in each set of drugs) which contains the drug name and number for this patient. The monitors should be notified of the process immediately. The investigators should record in CRF the reason and date of unblinding in detail and sign on the record. Once unblinded, the patient will have to be discontinued in this trial and treated as a dropout case.

### 9.3.4 The observer should provide the following information in SAE reports:

- ✧ Observer's name and center code
- ✧ Initials of the Subject's name
- ✧ Subject's general data including age, date of birth, marital status and body weight
- ✧ SAE details including descriptions of the affected body site, severity and the criteria for determining severity
- ✧ Description
- ✧ Occur date

- ✧ End date or duration of the AE
- ✧ Severity
- ✧ Treatment (including hospitalization)
- ✧ Causal relationship with the trial drug
- ✧ Outcome: recover or having sequelae
- ✧ Adjustment of drug treatment
- ✧ Measures taken for trial drug such as stopping treatment or continuing treatment, etc
- ✧ For life-threatening events, the cause of death and the possible relationship should be provided
- ✧ Autopsy findings
- ✧ Drug number
- ✧ Indication of the used drug or the trial drug
- ✧ Formula or concentration of the drug
- ✧ Daily dose and regimen
- ✧ Route of administration
- ✧ Other treatments: the investigators should provide information on the relevant products for concomitant drugs (including over-the-counter drugs) and non-drug therapies
- ✧ Other information: any information that can help understanding the events such as allergy, drug or alcohol dependence, family history, special examination findings.

## 10. Subject's withdrawal

10.1 Determination of withdrawal: any patient who has filled in the ICF and been enrolled into the clinical trial after screening has right to withdraw from this trial at any time; the subject will be regarded as withdrawal case as long as they has not completed the endpoint observation of this trial regardless of the withdrawal time and reasons.

### 10.2 Common causes for subject's withdrawal

#### 10.2.1 Withdrawal decided by the investigators

When it is no longer appropriate for the subjects to continue trial as a result of trial-emerged situations, the investigators can decide the withdrawal of the subject from this trial. The common reasons are as follows:

- ✧ A subject discrepant with the inclusion criteria were included by mistake
- ✧ Allergic reactions or disease deterioration which need emergency measures
- ✧ Poor compliance of a subject, who fails to use the study drug per requirements, and violate the trial protocol
- ✧ In the investigator's opinion, continuing the treatment is not to the patient's best interests (e.g. pregnancy)
- ✧ The efficacy can't be evaluated or the efficacy or safety evaluation is affected by reasons like data incompleteness, etc
- ✧ Unblinding or emergency unblinding
- ✧ It is inappropriate for the subjects to continue this trial due to AE or SAE

#### 10.2.2 Withdrawal decided by subjects

The subjects have rights to withdraw during this trial, or although the subjects did not explicitly request to withdraw from this trial, they will be regarded as "withdrawal" (or "dropout") cases if they no longer take the study drug or examination and consequently lost to follow-up. Efforts should be made to find out and record the reasons of withdrawal such as subjective perception of poor efficacy; finding it difficult to tolerate certain adverse reactions; too busy to continue this clinical study; economic reasons; or lost to follow-up for unexplained reasons.

#### 10.3 Handling of the withdrawal cases

The investigators should fill in the CRF with the withdrawal reasons, try best to contact the patients to complete the assessment items, fill in the last visit form, and record the last dosing time. For withdrawals due to AEs that have been eventually judged to be related to the trial drug through follow-ups, the investigators must record them in the CRF and notify the sponsor. CRF of the withdrawal cases must be retained regardless of their withdrawal reasons; the last assessment results will be carried forward to serve as the final results for full data analysis of the efficacy and adverse reactions.

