## 2. Trial purpose

This study is to evaluate the efficacy and safety of hemoporphin for injection for the treatment of port-wine stains using placebo as the control in two stages of PDT treatments. Primary endpoint will be established at the first stage, and safety analysis will include both stages.

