#### 6. Trial arrangement

- Treatments: up to 2 times (the patients can receive an additional treatment if the treatment area did not subside completely after the first treatment)
- Efficacy evaluation: the efficacy evaluation is carried out in Week 8 after each treatment; both

evaluations are compared to the disease conditions before the treatment.

- Laboratory examination: the testing is carried out before each treatment and on Day 4 after the treatment.

Trial Flowchart

|                                   | PDT treatment                 |       |                                |       | Efficacy observation                                        |
|-----------------------------------|-------------------------------|-------|--------------------------------|-------|-------------------------------------------------------------|
|                                   | The first course of treatment |       | The Second course of treatment |       | The first/second course of treatment
Week 8 of treatment |
|                                   | Day 1                         | Day 4 | Day 1                          | Day 4 |                                                             |
| Instructions for patients         | ×                             |       |                                |       |                                                             |
| Signing ICF                       | ×                             |       |                                |       |                                                             |
| Laboratory examination            | ×                             | ×     | ×                              | ×     |                                                             |
| Inclusion criteria                | ×                             |       |                                |       |                                                             |
| Exclusion criteria                | ×                             |       |                                |       |                                                             |
| History                           | ×                             |       |                                |       |                                                             |
| Accompanied diseases              | ×                             |       |                                |       |                                                             |

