### 14.1 Primary Populations

The primary efficacy variable will be summarized and analyzed in ITT and PP populations, the secondary efficacy variables will be summarized and analyzed in ITT populations. ITT population will be the primary analysis population.

✧ Full analysis set (FAS): refers to the set of eligible cases and dropout cases excluding the

rejected cases. The ITT population will be defined as all randomised patients having received at least one dose of either the tested or the reference treatments.

- ✧ Per protocol set (PPS): The PP population will be defined as all the subjects who completed the treatment period without any major deviation from the protocol.
- ✧ Safety set (SS): Safety population will be defined as all the subjects who received at least one treatment and have actual data of safety indexes.

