## 14.2 Statistical Analysis Method

### 14.2.1 Demographic Characteristics

(1) Consistency with normal distribution: Because this is a randomized and blinded trial with a large sample size, the data is acceptable when close to normal distribution. Appropriate statistical methods or data transformation will be adopted for non-normal distributed data, D method, W method or moment method will be used.

(2) Presence of outliers: statistical and clinical analysis should be carried out to determine the acceptance and rejection.

(3) Handling of the missing values of primary efficacy index: if the primary efficacy data of an individual subjects is missing, missing data were imputed as non-responses.

(4) Analysis of the subjects who did not complete this trial: the cause of each dropout case should be analyzed.

(5) Descriptive statistics: provide the mean, standard deviation, maximum, minimum, median, confidence interval, frequency (constituent ratio), etc.

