### 14.2.2 Statistical inference method

(1) Measurement data: t-test, paired t-test, rank sum test, paired rank sum test, median test method, etc.

(2) Numeration data: chi-square test, Fisher's exact test, etc.; Redit analysis and CMH method can be used to test the ranked data.

(3) Primary efficacy: The response rate will be analyzed using Cochran–Mantel–Haenszel test. Logistic regression analysis, with center and PWS type as covariates will be used to compare treatment group versus placebo group on primary efficacy. If baseline variables are not balanced between groups, non-balanced variable will be also included as covariates in the model. For response rate at week 8, missing data were imputed as non-responses.

(4) Difference analysis: in primary efficacy analysis, a 40% difference between the treatment and placebo group in response rate is expected to be detected.

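### Sections 10.3 and 14.2 give two incompatible rules for missing Week 8 efficacy in the same population, and carry-forward does not suit the safety data

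*Protocol*

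**What the plan says.** **Withdrawals.** Protocol section 10.1 defines these broadly: "the subject will be regarded as withdrawal case as long as they has not completed the endpoint observation of this trial". For all of them, section 10.3 asks sites to try to contact the patient, complete the assessments and fill in a last-visit form. It then says that "the last assessment results will be carried forward to serve as the final results for full data analysis of the efficacy and adverse reactions".

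**Missing primary data.** Section 14.2.1(3) says that "if the primary efficacy data of an individual subjects is missing, missing data were imputed as non-responses". Section 14.2.2(3) repeats it for the endpoint: "For response rate at week 8, missing data were imputed as non-responses".

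**Population.** Section 14.1 describes the FAS and the ITT population in a single bullet and makes ITT primary. Neither imputation rule is tied to a different set, and neither is called a sensitivity analysis.

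**Timing.** Section 2 says: "Primary endpoint will be established at the first stage, and safety analysis will include both stages". Section 6 adds that "the efficacy evaluation is carried out in Week 8 after each treatment". The flowchart schedules photographs on Days 1 and 4 of course 1 but no efficacy evaluation on Day 4. Under section 8.1 the expert panel rates efficacy from photographs.

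**Safety.** Section 14.1 limits the Safety set to "all the subjects who received at least one treatment and have actual data of safety indexes". Laboratory tests are done before each treatment and on Day 4 (section 6), and section 14.5 item 6 analyses shifts from normal to abnormal.

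**The concern.** Two rules are stated for one situation: a randomised, treated subject with no Week 8 result in course 1. Section 10.3 scores that subject on whatever was last assessed; section 14.2 scores the subject as a non-responder. Where the last assessment is a favourable early rating, an analyst cannot obey both.

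An early rating is also a weak stand-in for Week 8. Section 4.3 expects swelling, blisters and scabs at the irradiated site after treatment, and section 6 places the evaluation at Week 8. At stake are the primary response rates, their difference, and the 95% confidence interval that section 14.2.3 requires.

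Section 10.3 also extends carry-forward to adverse reactions. An event either occurred or did not in the period observed, so carrying a last status forward has no clear meaning. If the rule is read as covering laboratory values, it would supply a Day 4 result for someone never tested on Day 4.

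**Working it through.** **The plan's own figure.** Section 3.1 gives 66 + 22 subjects for 75% v 35%, two-sided α = 0.05, 90% power, 3:1. Enumerating Fisher's exact test at 66/22 gives power 90.3%, so the figure reproduces. The normal approximation gives 60 + 20 without continuity correction and 69 + 23 with it. The inputs can be used as stated.

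**Inputs.**
- Response among completers: 75% trial, 75 − 40 = 35% control (section 3.1).
- Planned size: 330 + 110 (section 3.1).
- Missing Week 8 results: 10% per arm. Section 12 gives 10% as the dropout ceiling. Placing all of it in course 1, equally by arm, is an assumption.
- Subjects affected: 330 × 0.10 = 33 and 110 × 0.10 = 11.

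**When the two rules differ.**

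| Subject | Carry-forward (10.3) | Non-response (14.2) |
|---|---|---|
| Leaves before Week 8 of course 1, only baseline available | No improvement: non-response | Non-response |
| Leaves before Week 8 of course 1, early photograph rated a response | Response | Non-response |
| Leaves in course 2 | Course 1 result already observed | Course 1 result already observed |

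Only the second row conflicts for the primary endpoint.

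**Non-response rule.**
- Trial: 0.75 × 0.90 = 0.675
- Control: 0.35 × 0.90 = 0.315
- Difference: 0.360

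**Carry-forward rule.** Let r₁ and r₀ be the shares of the missing trial and control subjects whose carried rating is a response. Then

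difference = (0.675 + 0.10 r₁) − (0.315 + 0.10 r₀) = 0.360 + 0.10 (r₁ − r₀).

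| r₁ | r₀ | Trial | Control | Difference |
|---|---|---|---|---|
| 0 | 0 | 67.5% | 31.5% | 36 points |
| 0.75 | 0.35 | 75.0% | 35.0% | 40 points |
| 0 | 1 | 67.5% | 41.5% | 26 points |
| 1 | 0 | 77.5% | 31.5% | 46 points |

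The last two rows are bounds. With r₁ = r₀ both arm rates move but the difference stays at 36. In the 40-point row about 33 × 0.75 ≈ 25 trial and 11 × 0.35 ≈ 4 control subjects change outcome, against a maximum of 33 + 11.

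**Interval and power.** Unadjusted, SE = √[p₁(1 − p₁)/330 + p₀(1 − p₀)/110], with interval d ± 1.96 SE:
- 36 points: SE 0.0512, interval 26.0 to 46.0. That this matches the range of point estimates is a coincidence.
- 26 points: SE 0.0536, interval 15.5 to 36.5.
- 46 points: SE 0.0499, interval 36.2 to 55.8.

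Power is lowest at 26 points. The pooled rate is (330 × 0.675 + 110 × 0.415)/440 = 0.61, and the null SE is √[0.61 × 0.39 × (1/330 + 1/110)] = 0.0537. Power = Φ[(0.26 − 1.96 × 0.0537)/0.0536] = Φ(2.89) ≈ 0.998.

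**Laboratory shifts (illustration).** The documents give no abnormality rate. Assume a true Day 4 conversion rate of 10%, with 10% of subjects missing Day 4 and given a normal pre-treatment value. The reported rate is 0.10 × 0.90 = 9%. In the other direction, carrying an unresolved event forward could overstate persistence.

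**The case against.** **The specific rule governs.** Section 14.2 addresses the primary index and Week 8 response by name, and does so twice; section 10.3 speaks of efficacy in general, which includes the investigator and subject ratings in 8.2. Non-response is the natural reading for the primary analysis. That is fair and it guides the fix, but the protocol does not say so, and 10.3 claims the full analysis of efficacy without exception.

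**The rules will usually agree.** No efficacy rating is scheduled before Week 8, and an early photograph showing treatment reactions is less likely to be rated a response. This stands, and it confines the conflict to one group of subjects. It does not remove it, because 10.3 itself prompts early last-visit assessments.

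**A reader might infer that the rule could be chosen after seeing results.** The documents do not support this. Section 14 finalises the statistical plan before database lock, and the further discussion in 13.4 comes before unblinding. The choice could be made late, but not with treatment-group results in view.

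**A reader might infer that carry-forward hides harm.** This does not follow either. Section 9.2.1 requires every AE to be recorded, 9.2.1 and 9.2.5 require follow-up of AE withdrawals until recovery or resolution, and nothing lets a recorded event be overwritten. Section 10.3 does not mention laboratory values, so the Day 4 point depends on reading it that way.

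**A reader might infer that unblinding creates missing outcomes.** Section 9.3.3 says: "Once unblinded, the patient will have to be discontinued in this trial and treated as a dropout case". But 10.3 already asks sites to complete assessments in withdrawn subjects, so dropout status alone does not make the Week 8 result missing. What is unstated is whether a result obtained that way is used.

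**Conclusion.** The contradiction is real and reaches the primary endpoint in the primary population. It changes a subject's outcome only when that subject leaves before Week 8 of course 1 and an early photograph or last-visit assessment is rated a response.

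Under the assumptions above, the choice of rule can move each arm's rate by up to 10 points, and the difference by up to 10 points either way from 36. The extremes need opposite carried ratings in the two arms; less than 10% missing in course 1 would shrink the range in proportion. The chance of a significant result is hardly affected. The reported effect and its interval are.

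On safety, the supported conclusion is narrow: carry-forward is ill-defined for adverse reactions, and if applied to laboratory shifts it conflicts with a Safety set that requires actual data.

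**What to change.** 1. In 10.3, delete the carry-forward sentence, or label it a sensitivity analysis for efficacy only, and refer to 14.2. State there that a missing Week 8 response in course 1 counts as non-response in the primary ITT analysis.
2. For safety, use observed data only: count all recorded AEs, and take subjects with a post-dose sample as the denominator for laboratory shifts.
3. State that a Week 8 photograph obtained after withdrawal or unblinding is rated by the panel and used in the ITT analysis. This concerns observation only, not whether treatment continues.

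The cost is wording, plus a Week 8 photograph in the withdrawn subjects who agree, which 10.3 already asks sites to attempt. No change to sample size or schedule is needed.

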### 11. Discontinuation of the trial

Trial discontinuation refers to stop of this whole clinical trial without completion per the trial protocol. The major purposes of trial discontinuation are to protect the subject's interests, ensure trial quality and avoid unnecessary financial loss. Trial discontinuation during the study can result from the following reasons:

- ☞ The investigators identify serious safety issues

- ☞ Very poor efficacy makes it unnecessary to continue this trial
- ☞ There are major defects in protocol design or major deviations during the implementation process
- ☞ The sponsor has budget or management difficulties
- ☞ The state's administrative department revokes this trial

The trial discontinuation can be temporary or permanent. When the trial is discontinued, all the trial records should be retained for future supervision.

## 12. Clinical trial quality control

During this study, all the clinical trial participants should implement the GCP principles and strictly follow the clinical protocol in observation and evaluation. The sponsor will dispatch clinical study monitors to inspect the trial progresses and CRF quality and give advice on the drugs and study-emerged issues.

- The participating investigators must receive uniform training and use uniform recording style and determination criteria.
- The entire clinical trial process should proceed under strict blinded condition.
- The investigators should record the contents of all raw data items accurately, carefully and in sufficient details, and fill in the CRF items accurately.
- All the observation results and findings in this clinical trial should be verified to guarantee the data reliability and ensure that all the conclusions of this clinical trial are derived from the raw data. Corresponding data management procedures should be in place in all stage of clinical trial and data processing.
- Active measures should be taken in case of potential dropout cases. The dropout rate should be controlled within 10%.
- All the study hospitals should maintain their quality control standards stringently, and the clinical monitors will carry out periodical monitoring.

## 13. Data management

See “data management plan” for details of data management. Before database lock, the data manager, principal investigator and sponsor will carry out blind review and discussion, and come into a final data management report. This protocol will only provide the general requirements for data management.

### 13.1 The filling and transfer of CRF

The completed CRF will be reviewed by the clinical investigators and monitors before transferring to the data statistical processing institution for data entry and management. All the processes should be documented properly.

